### Non-Photoplethysmography Data Preprocessing

All 7 non-photoplethysmography features required for downstream model training—age, gender, body weight, body height, meal timing, diabetes status, and family history of diabetes—were complete and free of errors. Automated blood test results and finger prick glucometer measurements also contained no missing or invalid values.

Medication status, collected via participant self-report, was manually curated by medical personnel. Other questionnaire data will be further cleaned or curated as needed for downstream analyses. Missing values, if encountered, can be addressed by tracing the source information or applying statistical methods, such as decision tree–based imputation.

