## Introduction

Diabetes mellitus (DM) is a major noncommunicable disease that has affected around 500 million people worldwide and continues to rise up to 700 million people globally in 2045 [1]. Other noncommunicable diseases’ death risks have decreased by 20% since the turn of the century; DM, in contrast, has increased by 3% worldwide. The latest International Diabetes Federation Diabetes Atlas (2025) reports that 11.1% of the adult population (20‐79 y) is living with diabetes, with over 4 in 10 unaware of their condition.

Several reports have projected that about 1 in 2 adult patients with diabetes are unaware of their diagnosis [1-3]. Undiagnosed DM has resulted in an increase of cases with complications and elevated the burden of the disease, as younger undiagnosed DM cases have more rapid progression of complications and lower response to general DM treatment. This has been shown to be higher in low- and middle-income countries, where 80% of the DM population lived, thus reflecting the enormous burden of the disease [4,5]. Meanwhile, early diagnosis and treatment of DM reduce the risk and slow the progression of debilitating complications such as amputation, vision loss, renal failure, cardiovascular disease, dementia, some cancers, and infections including tuberculosis and severe COVID-19 [6]. All of the above calls for early screening and frequent monitoring strategies that are both effective and cost-efficient.

Currently available methods to detect DM are hemoglobin A_1c_ (HbA_1c_) level, fasting plasma glucose, 2-hour glucose tolerance test, and random plasma glucose test. All these methods are invasive; they require trained professionals and laboratory equipment to be performed correctly. The American Diabetes Association has recommended DM screening starting at 35 years and every 3 years after, especially for people with obesity, overweight, and one risk factor [7]. In low- and middle-income countries, this is even harder to implement due to the cost and scarce resources of such screening methods [5,6,8].

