**Figure 1. F1:**
[figure not shown]
A conceptual framework of study design from recruitment, data collection, to discharge for 473 participants who self-acknowledged having diabetes mellitus (DM) and 412 participants who did not (non-DM).

Subsequently, each participant’s photoplethysmography data at the fasting time point (the first time point) were collected using both a smart ring (JC Smart Health Ring 2301B) and a smartwatch (Actxa Spark+Series 2), both provided by Actxa Pte Ltd. Simultaneously, blood samples were obtained from 2 sources: capillary blood for glucose concentration measurement using Accu-Chek (Roche) and plasma blood from the cubital vein for laboratory analysis, as described in a later section.

Participants then consumed a 552-kcal meal set with 79.8 g of carbohydrate content prepared by Ukrida Hospital. This meal was chosen to ensure adequate sustenance and satiety after overnight fasting, as sugary drinks alone may not sufficiently fulfill. The nutritional composition of the meal is detailed in Textbox 1 and Table S1 in Multimedia Appendix 1.

Textbox 1.Nutritional value of the set meal for the subjects, given after subjects fast for a minimum of 8 h and undergo first blood sample collection and photoplethysmography reading from wearables.Energy (kcal): 552.1Water (g): 241.8Protein (g): 19Protein percentage: 13.8Fat (g): 19.3Fat percentage: 31.5Carbohydrate (g): 79.8Carbohydrate percentage: 57.8Dietary fiber (g): 5.2Polyunsaturated fatty acid (g): 1.8Cholesterol (mg): 33Vitamin A (µg): 1396.8Carotene (mg): 0.4Vitamin E (eq.) (mg): 0.8Vitamin B1 (mg): 0Vitamin B2 (mg): 0.1Vitamin B6 (mg): 0.6Total folic acid (µg): 31.8Vitamin C (mg): 10.7Sodium (mg): 1015.5Potassium (mg): 549.4Calcium (mg): 59.2Magnesium (mg): 66.2Phosphorus (mg): 231.5Iron (mg): 2.5Zinc (mg): 1.6

Participants then underwent measurements at the second time point (1 h postprandial), third time point (2 h postprandial), and fourth time point (3 h postprandial). Photoplethysmography data collection followed the same procedure as the first time point using both the smartphone and the smart ring. For blood sample collection and testing, the third time point followed the same procedure as the first time point, with both capillary and plasma blood samples collected and analyzed. At the second and fourth time points, plasma blood collection was omitted, and only capillary blood samples were obtained and tested. Further details are provided in Table 1.

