### Photoplethysmography Data Feature Extraction

To accurately identify key temporal positions of the photoplethysmography waveform, potential systolic peaks were first detected using sign changes in the first-order difference of the photoplethysmography signal, specifically identifying transitions from positive to negative values. The leading and trailing troughs of the pulse wave were then detected by inverting the photoplethysmography signal and applying the same first-order difference and sign change method.

HR was then calculated using the key temporal positions. The measured HR was required to exceed 48 beats per minute. No recordings from this clinical trial were excluded based on this criterion.

Using the identified key temporal positions, a feature extraction module was then applied to the photoplethysmography data fragments to compute a comprehensive set of features. The panel of features was established in our previously reported model, which included 248 features related to HR, HR variability, waveform morphology, energy metrics, complexity measures, and continuous wavelet transform [12].

Prior to model training, feature selection techniques were applied to eliminate redundant features. This process was conducted exclusively on the feature set derived from photoplethysmography data and involved 2 stages. First, a self-correlation matrix was calculated, and features with a Pearson correlation coefficient >0.7 were removed to reduce multicollinearity. Second, the correlation between each remaining feature and the regression target—blood glucose levels measured via finger prick tests under different mealtime conditions—was assessed. A subset of features with the strongest correlations to the target variable was retained, with the final number determined empirically to optimize model performance.

To account for the varying feature magnitudes, Min-Max scaling was applied. Since the regression target (blood glucose values) exhibited a nonnormal distribution, a Box-Cox transformation was used for normalization. Following model prediction, an inverse Box-Cox transformation was performed to restore the predicted blood glucose levels to their original scale.

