### Model Training

During model training, 10-fold cross-validation was applied to obtain a robust estimate of generalization performance and to monitor potential overfitting. To prevent data leakage, particularly biometric identity-related features potentially embedded in the photoplethysmography data [26], we ensured that fragments from the same participant were not included in both the training and validation sets. Data collected in this clinical trial were used exclusively for model training and validation.

Additionally, given that this study employs short-term, mealtime prospective measurements of blood glucose profiles, we aim to leverage each participant’s individual blood glucose fluctuation pattern to explore prediction of diabetes risk or glucose levels and probable glycemia monitoring post meal. To achieve this, the photoplethysmography data from the 4 mealtime points for each participant will be combined into a time series, which will serve as input to a model trained to predict glucose levels or diabetes risk across all 4 points of the meal cycle. This approach allows the longitudinal aspect of the data—the participant-specific fluctuation pattern—to be fully utilized, potentially improving model performance and predictive accuracy.

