### Statistical Analysis

Demographic data for continuous variables will be presented as mean (SD), and categorical variables will be presented as count (percentage). Univariate analyses will be performed using *t* tests for independent groups for continuous variables and chi-square tests for categorical variables. Discriminations are assessed by plotting the receiver operating characteristic curve and calculating the area under the receiver operating characteristic curve (AUC) or *C* statistic. The accuracy of the prediction model will be analyzed using both Type I and Type II Parkes Error Grids. The sensitivity, specificity, and *F*_1_-score of the BGEM model will also be evaluated and presented to give a clear description of its strength and weakness.

The Parkes Error Grid is used to assess how clinically risky an inaccurate blood glucose reading might be. Each device reading is compared with a reference value and placed into 1 of 5 zones. Zone A means the reading is clinically accurate and would not change treatment. Zone B reflects small errors that might adjust a decision but have little or no impact on outcome. Zone C includes errors likely to affect clinical results. Zone D involves inaccuracies that could lead to clearly risky treatment decisions. Zone E represents dangerous errors that could cause severe or life-threatening consequences if acted upon [27].

The ML model will be trained using Lasso regression, cross-validation, and other ML techniques to find the optimal regularization parameter to ensure that the model generalizes to unseen data. The dataset is initially divided into a training set and a validation set. The training set is used for model development and hyperparameter tuning, while the validation set is reserved for a final, unbiased evaluation of the model’s performance. Analysis will ensure that the model does not overfit to the training data and is able to predict outcomes on new data with confidence. Once the optimal regularization parameter is identified through cross-validation, a final regression model is trained on the entire training set using this optimal regularization parameter value.

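### Self-reported diabetes status is a listed model input and diabetes risk a model output; nothing keeps them apart, so the plan permits circular or inflated diabetes-classification metrics

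*Protocol article*

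**What the plan says.** Five statements in the protocol article bear on this.

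- **Inputs.** Non-Photoplethysmography Data Preprocessing lists "age, gender, body weight, body height, meal timing, diabetes status, and family history of diabetes" and calls these seven variables "features required for downstream model training".
- **Source of status.** The Figure 1 caption shows that the split into 473 participants with and 412 without diabetes rests on what participants themselves acknowledged. Table 2 lists status as a questionnaire item.
- **Outputs.** Model Training describes "a model trained to predict glucose levels or diabetes risk across all 4 points of the meal cycle". The Discussion overview names evaluation of diabetes status as an aim beside glucose prediction. The only target defined explicitly, under Photoplethysmography Data Feature Extraction, is "the regression target—blood glucose levels measured via finger prick tests under different mealtime conditions".
- **Metrics.** Statistical Analysis states: "Discriminations are assessed by plotting the receiver operating characteristic curve". It adds AUC, sensitivity, specificity and F1, and Parkes error grids for accuracy. It names neither the binary outcome nor a reference standard for it.
- **Intended use.** The Abstract presents the tool for screening or monitoring, and the Introduction argues from projections that "about 1 in 2 adult patients with diabetes are unaware of their diagnosis".

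**The concern.** A variable that records whether the participant has diabetes is listed as a predictor, and diabetes risk is among the quantities to be predicted. The article does not say that the list applies only to the glucose regression, and it does not remove status when diabetes is the output. Feature selection is described as applied only to the photoplethysmography (PPG) features, so that step would not drop status. A Lasso penalty removes weak predictors, and here status would be a strong one.

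If the list is followed as written for a diabetes-risk model, the reported discrimination could come mainly from the participant's own answer and say little about the PPG signal. The participant-level split in the 10-fold cross-validation gives no protection, because the answer is supplied in the training and validation folds alike. At stake is whether any diabetes-classification figure from this dataset could support a screening claim.

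**Working it through.** **The plan's own calculation.** The only design figure is the sample size for limits of agreement. With 200 per group the half-width is 1.96 × √(3/200) = 0.240 SD, and 800/0.9 = 889, against about 890 stated. Both reproduce, and this point does not affect them. The article sets no target for AUC, sensitivity, specificity or F1.

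**Inputs for the check.** From the article: 885 participants, of whom 473 report diabetes, so q = 473/885 = 0.534. Assumed, because the article gives no figure: the agreement of self-report with a laboratory label (sensitivity Se, specificity Sp) and the AUC of the PPG signal by itself.

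**Case A: the label is self-reported status.** Predictor and label are the same variable. Se = Sp = 1, so AUC = (Se + Sp)/2 = 1.00 and F1 = 1.00 with no PPG data.

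**Case B: the label is laboratory-based.** For status as the only predictor:

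- AUC = (Se + Sp)/2
- label prevalence p = (q − (1 − Sp))/(Se + Sp − 1)
- PPV = Se × p/q
- F1 = 2 × Se × PPV/(Se + PPV)

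For Se = Sp = 0.9: p = (0.534 − 0.1)/0.8 = 0.543, PPV = 0.9 × 0.543/0.534 = 0.91, F1 = 0.91.

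| Assumed Se / Sp | AUC, status alone | p | F1, status alone |
|---|---|---|---|
| 0.95 / 0.95 | 0.95 | 0.538 | 0.95 |
| 0.90 / 0.90 | 0.90 | 0.543 | 0.91 |
| 0.80 / 0.80 | 0.80 | 0.557 | 0.82 |
| 0.60 / 0.70 | 0.65 | 0.782 | 0.71 |

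**Adding status to a PPG signal.** A simulation used 885 participants (473 reporting diabetes), one PPG score, penalised logistic regression, 10-fold cross-validation and 30 replicates. Mean cross-validated AUC without → with status:

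| Assumed PPG AUC | Label = self-report | Laboratory label, Se = Sp = 0.9 | Laboratory label, Se = Sp = 0.8 |
|---|---|---|---|
| 0.6 | 0.59 → 1.00 | 0.60 → 0.91 | 0.60 → 0.82 |
| 0.7 | 0.70 → 1.00 | 0.70 → 0.93 | 0.69 → 0.86 |

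**Undiagnosed people.** Everyone with undiagnosed diabetes answers no, as does everyone without diabetes. Among those who answer no the input is constant: Se = 0, Sp = 1, AUC = (0 + 1)/2 = 0.50. The gain from status shown above vanishes in the group that screening is meant to find.

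**The case against.** The strongest reply is that the article never says status enters a diabetes-risk model.

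- The sentence on preprocessing reports data completeness across all planned models. It could be a pooled list in which status is an input to the glucose regression and the label of the risk model.
- The only input named for the time-series model in Model Training is the series of PPG recordings from the four mealtime points.
- The metrics in Statistical Analysis are not said to be for diabetes.
- HbA1c and plasma glucose were measured and could supply the label.
- Monitoring people with known diabetes is also a stated purpose, and there status is a legitimate covariate for glucose.
- Per-model feature sets are commonly left to the full protocol.

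Much of this stands. A reader might infer that the planned AUC, sensitivity, specificity and F1 are circular as a matter of fact; the text does not establish that, because the outcome and its reference standard are unnamed. A reader might also infer that predicted glucose will be thresholded to classify diabetes, or that diabetes medication and year of diagnosis are model inputs. The article describes no such threshold, and neither variable is among the seven features. Nor has an inflated result been published here: the article gives no discrimination figure from this study.

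What does not stand is the view that this is only omitted detail. The article positively lists status as a required feature, separates features from the target elsewhere, mentions blood results apart from the list, and positively makes diabetes risk an output. Diabetes risk or status is also the only binary condition it names for prediction; it gives no glucose cut-off.

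**Conclusion.** The point holds as a conditional. The plan lists self-reported status as a training feature, makes diabetes risk or status an output, and contains nothing that separates the two. It therefore permits diabetes-classification metrics that are:

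- **circular**, with AUC, sensitivity, specificity and F1 of 1.00 from status alone, if the label is self-reported status;
- **inflated**, if the label is laboratory-based. Status alone gives an AUC of 0.80 to 0.90 for an assumed sensitivity and specificity of self-report of 0.8 to 0.9, and 0.65 to 0.95 over the wider range tried.

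The 1.00 follows by construction. The other figures illustrate size and rest on assumed agreement and assumed PPG signal, not on data from the study. Under either label the result would not carry over to undiagnosed people. Use of status in a glucose regression for people with known status is not circular and is not criticised.

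**What to change.** 1. State that diabetes status is excluded from the inputs of every model that outputs diabetes risk or status or supports a screening claim. Apply the same rule to direct proxies, such as diabetes medication or year of diagnosis, should they ever be added.
2. Name the binary outcome for ROC/AUC, sensitivity, specificity and F1, and define its label from the HbA1c and plasma glucose already measured. Say how participants with reported diabetes whose laboratory values fall below the chosen limits are labelled.
3. Report classification performance in the 412 participants who did not report diabetes, with confidence intervals. The article does not say how many of them would be laboratory-positive. Under the assumptions above the number is 885 × p × (1 − Se): 885 × 0.543 × 0.1 ≈ 48 for Se = Sp = 0.9, and 885 × 0.557 × 0.2 ≈ 99 for Se = Sp = 0.8. Sensitivity there may be imprecise.
4. Status may stay as an input to the glucose-monitoring regression, reported separately by diabetes status and with no screening claim.

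No new data are needed. The cost is a revised feature list, a re-fit and probably a lower reported discrimination.

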### Photoplethysmography Data Preprocessing

Each photoplethysmography recording was required to be at least 4 minutes in duration. No recordings from this clinical trial were excluded based on this criterion.

One participant was absent for the fourth measurement (3 h after the meal). For this participant, the available time point data were retained for individual data point analyses. However, in the time-series analysis (see the section photoplethysmography Data Feature Extraction), the data were excluded due to the incomplete sequence.

Raw photoplethysmography signals were obtained from the smartwatch (16-bit binary) and smart ring (23-bit binary) devices. Raw photoplethysmography data were preprocessed using a previously developed pipeline incorporating frequency noise filtering and outlier correction [12].

During the signal preprocessing stage, the raw digital signals were first converted to analog values using the following formula:

$V_{i}=5\;\times \frac{Signal}{2^{16}}$  (for smartwatch data)

$V_{i}=5\;\times \frac{Signal}{2^{23}}$  (for smart ring data)

A Chebyshev Type II bandpass filter (0.3‐5 Hz) was applied to remove low- and high-frequency noise, including motion artifacts. Outliers were identified, when necessary, using a *z* score threshold of 3 SD from the mean and replaced with reasonable estimates via nearest-neighbor interpolation prior to HR variability feature extraction.

### Photoplethysmography Data Feature Extraction

To accurately identify key temporal positions of the photoplethysmography waveform, potential systolic peaks were first detected using sign changes in the first-order difference of the photoplethysmography signal, specifically identifying transitions from positive to negative values. The leading and trailing troughs of the pulse wave were then detected by inverting the photoplethysmography signal and applying the same first-order difference and sign change method.

HR was then calculated using the key temporal positions. The measured HR was required to exceed 48 beats per minute. No recordings from this clinical trial were excluded based on this criterion.

Using the identified key temporal positions, a feature extraction module was then applied to the photoplethysmography data fragments to compute a comprehensive set of features. The panel of features was established in our previously reported model, which included 248 features related to HR, HR variability, waveform morphology, energy metrics, complexity measures, and continuous wavelet transform [12].

Prior to model training, feature selection techniques were applied to eliminate redundant features. This process was conducted exclusively on the feature set derived from photoplethysmography data and involved 2 stages. First, a self-correlation matrix was calculated, and features with a Pearson correlation coefficient >0.7 were removed to reduce multicollinearity. Second, the correlation between each remaining feature and the regression target—blood glucose levels measured via finger prick tests under different mealtime conditions—was assessed. A subset of features with the strongest correlations to the target variable was retained, with the final number determined empirically to optimize model performance.

To account for the varying feature magnitudes, Min-Max scaling was applied. Since the regression target (blood glucose values) exhibited a nonnormal distribution, a Box-Cox transformation was used for normalization. Following model prediction, an inverse Box-Cox transformation was performed to restore the predicted blood glucose levels to their original scale.

### Model Training

During model training, 10-fold cross-validation was applied to obtain a robust estimate of generalization performance and to monitor potential overfitting. To prevent data leakage, particularly biometric identity-related features potentially embedded in the photoplethysmography data [26], we ensured that fragments from the same participant were not included in both the training and validation sets. Data collected in this clinical trial were used exclusively for model training and validation.

Additionally, given that this study employs short-term, mealtime prospective measurements of blood glucose profiles, we aim to leverage each participant’s individual blood glucose fluctuation pattern to explore prediction of diabetes risk or glucose levels and probable glycemia monitoring post meal. To achieve this, the photoplethysmography data from the 4 mealtime points for each participant will be combined into a time series, which will serve as input to a model trained to predict glucose levels or diabetes risk across all 4 points of the meal cycle. This approach allows the longitudinal aspect of the data—the participant-specific fluctuation pattern—to be fully utilized, potentially improving model performance and predictive accuracy.

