**Objective:**

The aim of this study is to collect a large and more diverse dataset for the training of BGEM machine learning models. This dataset is intended to improve the model’s generalizability and to evaluate its performance across different age groups, racial groups, and skin types, with the goal of enhancing accuracy and robustness for diabetes risk assessment and glucose monitoring.

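### The exploratory time-series model estimates fasting, 1 h and 2 h glucose partly from later recordings, so its accuracy at those points is retrospective and should not be read as concurrent monitoring accuracy

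*Protocol article*

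**What the plan says.** The protocol article, Methods, Model Training, describes a second model in addition to the main one. Its input is fixed: each participant's recordings from all four mealtime points "will be combined into a time series, which will serve as input to a model trained to predict glucose levels or diabetes risk". Its output is equally broad: it is "a model trained to predict glucose levels or diabetes risk across all 4 points of the meal cycle". The stated purpose is "to explore prediction of diabetes risk or glucose levels and probable glycemia monitoring post meal", and the article expects that using the participant's own fluctuation pattern may improve performance. The abstract gives the aim of the whole dataset as improving the algorithm "with the goal of enhancing accuracy and robustness for diabetes risk assessment and glucose monitoring".

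Photoplethysmography Data Preprocessing reports that one participant missed the 3 h measurement. For the time-series analysis, "the data were excluded due to the incomplete sequence"; elsewhere, "the available time point data were retained for individual data point analyses". So the article separates a time-series analysis from single-time-point analyses.

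Statistical Analysis plans Parkes Error Grids (types I and II) for accuracy. It explains the grid as grading each device reading against a reference by its likely effect on treatment decisions. It does not say to which of the two models the grids apply.

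**The concern.** If the whole sequence is the input and glucose at every point is the output, the estimate at an early time point uses recordings that did not exist at that time. A wearable giving a reading 1 h after a meal has no 2 h or 3 h recording.

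Two things are at stake. First, any gain of the time-series model over the single-time-point model would mix genuine use of the participant's history with use of later data, and the design as described could not separate them. Second, an error grid treats each value as a reading that could be acted on. Applied to full-sequence estimates at fasting, 1 h and 2 h, it would describe an accuracy that concurrent use could not reproduce.

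The leakage safeguard in Model Training does not address this. It keeps a participant's data from appearing in both training and validation sets, whereas the look-ahead lies within one participant's own sequence. Cross-validation and a held-out set would both carry it through.

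**Working it through.** **No stated figure is contested.** The article gives no performance figure for this model. Its one derived figure, the sample size, reproduces (1.96 × √(3/200) = 0.240 SD for 200 per group) and is not affected.

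**Step 1: which outputs use later recordings.** The time points are fasting, 1 h, 2 h and 3 h after the meal (Methods, Study Design). With the full sequence as input:

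- fasting glucose uses 3 later recordings (1 h, 2 h, 3 h);
- 1 h glucose uses 2 (2 h, 3 h);
- 2 h glucose uses 1 (3 h);
- 3 h glucose uses none.

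That is 3 of 4 outputs. With 885 − 1 = 884 complete sequences, it is 884 × 3 = 2652 of 884 × 4 = 3536 glucose estimates per device.

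**Step 2: does the rest of the text fit this reading?** A model limited to current and earlier recordings could still have produced fasting, 1 h and 2 h estimates for the participant who missed only the 3 h measurement. That participant was instead removed from the time-series analysis, which fits a model that needs all four recordings. Nothing in the article limits the input for a given time point to what was available by then.

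**Step 3: illustration of size, on assumed values only.** Let glucose G at the four points have unit variance and equal correlation ρ between points. Let each recording act as X = G + noise, with noise variance v = 1/r² − 1, so that r is its correlation with concurrent glucose. For the best linear prediction of one glucose value from its own recording and m − 1 others,

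R² = [1 + (m − 1)ρ² − ρ(1 + (m − 1)ρ)² / (a + mρ)] / a, where a = 1 − ρ + v.

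Take r = 0.4, so v = 1/0.16 − 1 = 5.25.

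- For ρ = 0.6, a = 5.65. With m = 4: [2.08 − 0.6 × 2.8² / 8.05] / 5.65 = 0.265.
- For ρ = 0.8, a = 5.45. With m = 4: [2.92 − 0.8 × 3.4² / 8.65] / 5.45 = 0.340.
- For m = 1, R² = r² = 0.16 in both cases.

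The fair comparator at each point is the current recording plus all earlier ones (m = 1, 2, 3, 4 in turn). Ranges run from ρ = 0.6 to ρ = 0.8:

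| Output | Current and earlier recordings | All four recordings | Difference due to later recordings |
|---|---|---|---|
| Fasting | 0.16 | 0.26-0.34 | 0.10-0.18 |
| 1 h | 0.20-0.23 | 0.26-0.34 | 0.06-0.11 |
| 2 h | 0.24-0.29 | 0.26-0.34 | 0.03-0.05 |
| 3 h | 0.26-0.34 | 0.26-0.34 | 0 |

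The difference is largest at fasting, which is before the meal, and shrinks afterwards. At 1 h and 2 h, part of the gain over a single recording (0.16) is real use of history: at 1 h with ρ = 0.6, about 0.04 of the 0.10 gain (0.16 to 0.20) is history and about 0.06 (0.20 to 0.26) is look-ahead.

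**The case against.** A reader might infer that the plan promises real-time readings from this model and that the promise fails. The text does not support that. The aim is worded as exploration and the monitoring as probable, and nowhere is it said that a fasting, 1 h or 2 h value from this model is delivered when the recording is made. The abstract's monitoring goal belongs to the dataset as a whole. The article also motivates multi-point data by glycemic variability, a property of the whole profile, and a profile reconstructed after the cycle may properly use all four recordings. The single-time-point analyses are kept, and no passage says that the time-series result will replace them or be pooled with them.

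Further, the architecture is not given. The wording leaves open whether glucose or diabetes risk is the target, and a model that uses only past inputs is not strictly excluded. Such detail often sits in a full protocol or analysis plan that is not shown here.

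Most of this stands, and it limits the point to how the glucose estimates are labelled and used. It does not remove it. The article does state the input and the output, the complete-sequence exclusion fits that statement, the model is linked to post-meal monitoring, and the planned error grids treat estimates as device readings without distinguishing the two models.

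**Conclusion.** The point holds in a limited form. As described, the time-series model's glucose estimates at fasting, 1 h and 2 h are retrospective profile estimates, and their accuracy should not be presented as concurrent monitoring accuracy. The 3 h output, diabetes-risk prediction and the single-time-point analyses are unaffected. It would be wrong to infer that the accuracy of BGEM in general is compromised, or that data leak between participants.

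On size, the illustration puts the R² difference at 0.10-0.18 at fasting, 0.06-0.11 at 1 h and 0.03-0.05 at 2 h. These figures rest wholly on the assumed r = 0.4, ρ = 0.6 to 0.8, linear prediction, and equal correlation between fasting and post-meal values. The direction at the first three points follows from the design; the amounts are not estimates for this dataset. The conclusion also assumes that monitoring means a reading available when it is taken, and that the model is built as the article describes. This is a cheap improvement to an exploratory analysis, not a defect in the main one.

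**What to change.** In Methods, Model Training:

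- Add a version of the time-series glucose model whose input at each time point is limited to recordings at or before that point.
- State that this version, or the single-time-point model, supplies any accuracy offered for monitoring, including the Parkes Error Grids.
- Keep the full-sequence model for diabetes risk, and report its glucose estimates separately, labelled as retrospective profile reconstruction.

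Statistical Analysis should then name the model to which each error grid applies.

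The cost is one extra model fit, with no new data. The downside is that time-series accuracy will probably look less favourable at the first three time points.
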